### Plans to give access to the full protocol, participant-level data, and statistical code {31c}

The dataset, protocol, and statistical code (if applicable) will be made available to appropriately qualified investigators upon reasonable request to the principal investigator. The research team will have exclusive use of the data for a period of 12 months from the end of the project or until the data is published.

### Oversight and monitoring

#### Composition of the coordinating center and trial steering committee {5d}

Research staff from the Children’s Physical Activity Research Group (CPARG) at the Queensland Centre for Children’s Health Research in Brisbane will provide study coordination services and be responsible for the day-to-day running of the trial. The Research Support Officer from CPARG will review the eligibility, enrollment, and consent for each participant; independently verify data entered into REDCap; assign the participants to groups using the REDCap randomization module; monitor the assessment time points for scheduling; and review the data for completeness. The Research Project Officer from CPARG will independently review the data from the study assessments and exercise sessions, maintain the assessment equipment, support the research assistants and instructors, and oversee the exercise site organization. A trial steering committee comprising the chief investigators and associate investigators from each site will meet monthly via a videoconference in the first year, and quarterly in study years two through four of the trial, to ensure protocols are properly established and implemented and that project milestones are completed on time.

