#### Recruitment {15}

Participants will be recruited from the respiratory clinics at each study site (QCH, GCUH, RDH). On regularly scheduled clinic days, the clinic manager or research nurse will provide the study coordinator an appointment list of patients with a diagnosis of bronchiectasis ≥ 4 and < 13 years of age. To assess the initial eligibility, families will be asked a series of questions addressing the inclusion and exclusion criteria. Eligible and interested families will be given a participant information sheet and consent form. Following eligibility screening, the attending physician will confirm patient eligibility and provide medical clearance for exercise. To support recruitment, the exercise program will be delivered in local community halls with free parking. The exercise program will also be open to siblings and friends.

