#### Allocation concealment mechanism {16b}

Participants will be centrally randomized using the randomization module in REDCap [43]. A member of the research team (Research Support Officer) not involved in the delivery of the exercise intervention or the outcome assessments will be given sole privileges to the REDCap randomization module and dashboard. Allocation concealment will be ensured as the other members of the research team, including the chief investigators, will not be given access to the randomization module or the treatment allocation codes.

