#### Implementation {16c}

Prior to the commencement of the trial, the randomization schedule will be generated by an independent statistician. Participants will be enrolled in the study by the research staff responsible for recruitment in clinics. Following enrollment, the Research Support Officer will create a REDCap record for each enrolled participant. Following completion of the baseline assessment, the Research Support Officer will assign participants to groups using the REDCap randomization module. Once randomized, the research staff will notify the families of group allocation.

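### The officer who alone controls the randomization module also reviews each child's eligibility and consent, so concealment at that review is not secured as written

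*Protocol article*

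**What the plan says.** Allocation concealment mechanism {16b} places the randomization module with one person. The Research Support Officer "will be given sole privileges to the REDCap randomization module and dashboard". Concealment is then said to follow because the rest of the team, chief investigators included, "will not be given access to the randomization module or the treatment allocation codes". The only separation of duties stated for the officer is that this person is "not involved in the delivery of the exercise intervention or the outcome assessments".

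Composition of the coordinating center and trial steering committee {5d} lists the officer's tasks in one sentence. The officer "will review the eligibility, enrollment, and consent for each participant" and will also "assign the participants to groups using the REDCap randomization module".

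Other sections place the entry steps with other people. Under Recruitment {15}, "the attending physician will confirm patient eligibility and provide medical clearance for exercise". Under Implementation {16c}, "Participants will be enrolled in the study by the research staff responsible for recruitment in clinics", and "the randomization schedule will be generated by an independent statistician" before the trial starts. After enrollment the officer creates the REDCap record, and after the baseline assessment the officer assigns the group. Sequence generation {16a} gives 1:1 allocation, stratified by site, in random permuted blocks of 2, 4 or 6.

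**The concern.** Concealment protects against selection only if anyone who can query, hold back or return a child before assignment cannot anticipate which arm comes next. The plan rests its assurance on keeping everyone except the Research Support Officer out of the module. It then gives that one person a review of eligibility and consent for every child, and the stated separation of duties does not reach that review.

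Two of the criteria in Eligibility criteria {10} call for judgement: whether a child cooperates and understands well enough, and whether the family can attend sessions. The second bears more on the exercise arm, because only that arm has weekly sessions during follow-up. If a query or delay at the review step depended, even unconsciously, on the expected arm, the groups could differ at entry in ways that adjustment for age and sex would not reliably remove.

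**Working it through.** The protocol states no figure on this point, so there is none to reproduce. The check has two parts: the roles, and how far past assignments predict the next one.

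**Roles side by side**

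| Step | Who | Module access |
|---|---|---|
| Schedule generated ({16c}) | Independent statistician | None stated |
| Eligibility confirmed ({15}) | Attending physician | None stated |
| Enrollment ({16c}) | Clinic recruitment staff | Denied ({16b}) |
| REDCap record created ({16c}) | Research Support Officer | Sole holder |
| Eligibility, enrollment and consent reviewed ({5d}) | Research Support Officer | Sole holder |
| Group assigned ({16c}, {5d}) | Research Support Officer | Sole holder |

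The review has no stated time. In {5d} it is listed before assignment, and assignment waits for the baseline assessment, so there is room for a review finding to act before a child is randomized. No section says that the review is closed before the module is opened.

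**Predictability from past assignments**

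Inputs: block sizes 2, 4 and 6, stratification by site and 1:1 allocation, all from {16a}. Equal probability of the three block sizes is an assumption, because the protocol does not give the mix. The officer makes every assignment and so knows every past one at each site.

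The guessing rule is to name the arm that is behind at that site, and to toss a coin when the arms are level. Completed blocks are balanced, so the running difference at a site equals the difference within the current block. The rule therefore works without knowing the block sizes.

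For a block of size 2m, the expected number of correct guesses is m + 2^(2m−1)/C(2m, m) − 1/2.

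- Size 2 (m = 1): 1 + 2/2 − 0.5 = 1.50, and 1.50/2 = 75.0%.
- Size 4 (m = 2): 2 + 8/6 − 0.5 = 2.83, and 2.83/4 = 70.8%.
- Size 6 (m = 3): 3 + 32/20 − 0.5 = 4.10, and 4.10/6 = 68.3%.
- Equal mix: (1.50 + 2.83 + 4.10)/(2 + 4 + 6) = 8.43/12 = 70.3%.

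Whatever the mix, the figure lies between 68.3% and 75.0%. A simulation of a single stratum of 174 with equal block-size probabilities gave 70.2%, which agrees.

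Someone who also knew the block sizes would be certain of an assignment once one arm in the block is used up. The expected number of such assignments per block is 2m/(m + 1), that is 1, 4/3 and 3/2. This gives (1 + 1.333 + 1.5)/12 = 31.9%, and the simulation gave 32.0%. The protocol does not say that the officer knows the block sizes.

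The 70% refers to the next open slot at a site. If other children at that site are waiting between review and assignment, the prediction for the child under review is weaker.

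**The case against.** The strongest reply is that the entry decisions lie elsewhere. The family is screened in clinic, the attending physician confirms eligibility and gives clearance, and recruitment staff enroll. None of them is given the module. The officer's task is worded as a review, in a list of coordination and data checks, and no section gives the officer power to reject, delay or overturn an entry. Selective entry by this route would mean obstructing a child who has already been enrolled and cleared. User rights and record locking are also the kind of detail that an article leaves to the full protocol.

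Much of this stands, and it rules out two stronger readings. A reader might infer that the officer sees the next allocation, because everyone else is denied the codes and the statistician is said only to generate the schedule. That does not follow. By implication the officer holds the codes, but the protocol does not say who loads the schedule or whether unassigned allocations are displayed. Certain knowledge of the next arm is therefore not established. A reader might also infer that entry decisions in general are unconcealed, or that the assurance in {16b} is false. The documents do not support that either, because the people described as making entry decisions are kept from the module.

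The reply does not remove the overlap itself. The article assigns both roles to one person in plain terms, so this is not a complaint about missing detail. Reviewing each participant's eligibility and consent has little purpose unless a problem found there can lead to a query. The officer's knowledge of past assignments comes from making them and does not depend on how the module is configured.

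**Conclusion.** The point holds in a limited form. The protocol gives one officer both sole control of the randomization module and the review of each child's eligibility, enrollment and consent, and its stated separation of duties does not cover that combination. The officer can anticipate the next assignment at a site about 70% of the time from past assignments alone, about 20 percentage points above chance. This assumes equal block-size probabilities (68% to 75% for any mix) and that the child under review takes the next slot.

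Concealment at the review step is thus not secured as written, which is different from saying that it is broken. No effect on the primary result can be derived, because the documents do not say how often the review leads to a query or what the officer may do with one. The finding concerns a weakness in safeguards that is cheap to close.

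**What to change.** In section {5d}, give the eligibility and consent review to existing staff who have no access to the randomization module. At the least, require it to be completed and locked in REDCap before the module is opened for that child, with no return or rejection of the record afterwards. In section {16b}, limit the Research Support Officer to randomizing a record, with no view of unassigned allocations, and extend the stated separation of duties to entry.

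Hiding unassigned allocations would not be enough alone, because past assignments remain known to the officer. The lock has the same limit: it stops a child being reconsidered once the module is open, but the reviewer still knows what has gone before. Moving the review is therefore the stronger option.

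The cost is a change of user rights, one reassigned task, minor retraining and a short amendment. If the new reviewer also recruits, the check loses some independence. The lock-before-randomization option avoids that loss.

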#### Composition of the data monitoring committee, its role, and reporting structure {21a}

A data monitoring committee was deemed unnecessary as the study is relatively short in duration and does not involve significant safety concerns, risks to participants, or complexity.

#### Adverse event reporting and harms {22}

Surveillance for adverse will occur for the duration of the exercise program. Any minor adverse event (e.g., as minor injury) associated with participation in the therapeutic exercise program will be screened on a weekly basis by the exercise therapists by verbal questioning and recorded on the session checklist. Risk assessments with mitigation strategies will be completed prior to implementing the therapeutic exercise program. It will be the responsibility of the chief investigator to ensure that all adverse events, including serious adverse events (SAEs) events, are documented and accurately reported. All the study staff will be trained in the requirements and procedures of SAE and medically significant event documentation and reporting.

Serious adverse events (SAEs) are not anticipated given the low-risk exercise intervention but are defined as an experience that results in death, is life-threatening, requires unexpected in-patient hospitalization or prolongation of existing hospitalization, or results in persistent or significant disability/incapacity. Potential adverse events (AEs) associated with physical activity may include a fall, minor injury, exacerbation of existing symptoms, muscle soreness, or impact from sporting equipment. A protocol-related adverse event is an AE occurring during the study that is not related to the intervention but is considered by the investigator or medical monitor to be related to the research conditions, i.e., related to the fact that a subject is participating in the study. This may include AEs due to study procedures such as clinical diagnostic procedures.

Any SAE must be reported to the chief investigator within 24 h of becoming aware of the event. The project manager will complete the SAE form with as much information regarding the event that is available to them at the time. Telephone reports will be followed by a full report including copies of relevant medical records and other documents. SAEs are to be reported to the HREC within 24 h of notification. Follow-up reports must also be forwarded to the HREC as specified by the relevant HRECs in each jurisdiction. Participants and/or the infant’s primary carer will be asked to notify the study coordinators of any serious adverse events (SAEs) that may occur during the active study period.

#### Frequency and plans for auditing trial conduct {23}

A Project Management Group comprising the chief investigators and associate investigators at each site will meet monthly to review the trial conduct. These meetings will include the research staff from all sites. For quality assurance purposes and program fidelity, exercise therapists will complete a brief checklist after each session for the purposes of evaluating adherence to the program “essential elements” and to note any issues or difficulties encountered during the session. Additionally, the senior exercise therapist will complete on-site observations of program delivery on a quarterly basis. To monitor fidelity to the home-based program, parents/carers will complete a weekly training log provided at the first session.

#### Plans for communicating important protocol amendments to relevant parties (e.g., trial participants, ethical committees) {25}

Protocol amendments will be submitted to the lead ethics committee for review. The amended protocol will be distributed to sites by the Research Support Officer and updated on the clinical trial registry (ANZCTR).

#### Dissemination plans {31a}

The results of the BREATH trial will be disseminated through peer-reviewed journal publications, conference presentations, and via the ANZCTR.

## Discussion

Pediatric BE is a significant contributor to global mortality, morbidity, and healthcare utilization, yet there is a paucity of research on non-pharmaceutical interventions that aim to improve HR-QoL and impact disease progression for this population [1–3, 6]. It has been established that children with BE have delayed FMS proficiency leading to insufficient physical activity for health benefits [18]. A pilot RCT involving 21 children with BE demonstrated that a therapeutic exercise program is feasible and potentially efficacious in improving FMS proficiency and fitness [19]. A larger, fully powered RCT is now needed to determine the long-term impacts of the program, specifically the effects on acute exacerbations and HR-QoL.

This multi-center RCT will establish and test a highly scalable, therapeutic exercise program to reduce the proportion of children with no exacerbations of BE over 12 months and improve movement competency, HR-QoL, and exercise capacity. Improvements in these outcomes are likely to have an immediate positive impact on physical functioning, quality of life, and future health. BE exacerbation is the only known risk factor for lung function decline in this patient group. Thus, reducing the frequency of exacerbations during childhood through therapeutic exercise may be an important clinical management strategy for preventing a future decline in lung function and respiratory morbidity later in life.

This RCT is significant because it is the first fully powered RCT to test the effects of a therapeutic exercise program to prevent exacerbations and improve FMS proficiency, fitness, and HR-QoL in children with BE. By implementing a developmentally appropriate, play-based exercise program tailored to the individual needs of children with BE, the results have the potential for a major paradigm shift in the way in which therapeutic exercise is prescribed and implemented in children with chronic respiratory conditions. The exercise program can be readily translated. It does not require expensive equipment and can be delivered in a variety of settings, including the participant’s home. The program of research has strong potential for translation to other pediatric patient groups with similar needs for exercise therapy, including those with obesity, childhood cancers, and neurological conditions such as cerebral palsy. While exercise is well recognized to be universally beneficial, this RCT is required because it will provide long overdue level 1 evidence regarding the efficacy and cost-effectiveness of tailored therapeutic exercise programs for children with BE.

## Trial status

The recruitment of participants commenced at all study sites on the 17 February 2021 and is planned to continue until 30 June 2022 (protocol version 4, 10 August 2021).

## Abbreviations

AE: Adverse event
ANZCTR: Australian and New Zealand Clinical Trials Register
BE: Bronchiectasis
BMI: Body mass index
BREATH: Bronchiectasis - Exercise as Therapy
CCHR: Centre for Children’s Health Research
CCQoL: Chronic cough QoL
CF: Cystic fibrosis
CPARG: Children’s Physical Activity Research Group
CRS: Case report from
CSLD: Chronic suppurative lung disease
FEV1: Forced expiratory volume in 1 s
FMS: Fundamental movement skill
FVC: Forced vital capacity
GCUH: Gold Cold University Hospital
HRCT: High-resolution chest tomography
HR-QoL: Health-related quality of life
ICC: Intraclass correlation coefficient
MAR: Missing at random
MCMC: Markov chain Monte Carlo
MST: Modified shuttle test
MVPA: Moderate-to-vigorous intensity physical activity
PA: Physical activity
PedsQL™: Core Scales of the Pediatric Quality of Life Inventory
PMSC: Pictorial Scale of Perceived Movement Skill Competence
QCH: Queensland Children’s Hospital
QOL: Quality of life
RDSS: Research Data Storage Service
REDCap: Research Electronic Data Capture
RCT: Randomized controlled trial
RDH: Royal Darwin Hospital
SAE: Serious adverse events
TGMD-2: Test of Gross Motor Development 2nd Edition
